# Cost talk: protocol for a stepped-wedge cluster randomized trial of an intervention helping patients and urologic surgeons discuss costs of care for slow-growing prostate cancer during shared decision-making

**DOI:** 10.1186/s13063-021-05369-4

**Published:** 2021-06-29

**Keywords:** Stepped-wedge cluster randomized trial, Costs of care, Prostate cancer, Shared decision-making, Clinical communication, Financial toxicity, Cost conversations

## Abstract

**Background:**

Costs of care are important to patients making cancer treatment decisions, but clinicians often do not feel prepared to discuss treatment costs. We aim to (1) assess the impact of a conversation-based decision aid (Option Grid) containing cost information about slow-growing prostate cancer management options, combined with urologic surgeon training, on the frequency and quality of patient-urologic surgeon cost conversations, and (2) examine the impact of the decision aid and surgeon training on decision quality.

**Methods:**

We will conduct a stepped-wedge cluster randomized trial in outpatient urology practices affiliated with a large academic medical center in the USA. We will randomize five urologic surgeons to four intervention sequences and enroll their patients with a first-time diagnosis of slow-growing prostate cancer independently at each period. Primary outcomes include frequency of cost conversations, initiator of cost conversations, and whether or not a referral is made to address costs. These outcomes will be collected by patient report (post-visit survey) and by observation (audio-recorded clinic visits) with consent. Other outcomes include the following: patient-reported decisional conflict post-visit and at 3-month follow-up, decision regret at 3-month follow-up, shared decision-making post-visit, communication post-visit, and financial toxicity post-visit and at 3-month follow-up; clinician-reported attitudes about shared decision-making before and after the study, and feasibility of sustained intervention use. We will use hierarchical regression analysis to assess patient-level outcomes, including urologic surgeon as a random effect to account for clustering of patient participants.

**Discussion:**

This study evaluates a two-part intervention to improve cost discussions between urologic surgeons and patients when deciding how to manage slow-growing prostate cancer. Establishing the effectiveness of the strategy under study will allow for its replication in other clinical decision contexts.

**Trial registration:**

ClinicalTrials.govNCT04397016. Registered on 21 May 2020

**Supplementary Information:**

The online version contains supplementary material available at 10.1186/s13063-021-05369-4.

## Background

Financial toxicity refers to patients’ distress resulting from the costs of cancer care [1]. Direct and indirect treatment costs contribute to financial toxicity among people with cancer [2, 3]. Financial toxicity is associated with both poorer clinical outcomes [1, 4, 5] and poorer quality of life in cancer survivors [6, 7] and has an impact for many years after diagnosis [8]. Many patients with cancer report financial toxicity [8]. Its prevalence has made addressing the costs of care a priority for patients [9] and healthcare organizations [10, 11].

Patient-clinician discussions about treatment costs can help lower costs of care and reduce financial toxicity [1]. Patients welcome opportunities to discuss treatment costs with their clinicians [9, 12], but few patients and clinicians engage in cost conversations in routine practice [13–15]. As a result, many patients with prostate cancer pay more for their treatment than they expected [16]. While clinicians acknowledge the importance of addressing financial toxicity [17], they feel underprepared to initiate or lead cost conversations [13].

Preparing clinicians for cost discussions is an important component of reducing patients’ financial toxicity. After addressing costs during treatment discussions, clinicians can seek support from other professionals, such as social workers or financial navigators, to provide details about personal costs based on insurance and health needs [18]. Referring the patient for additional advice is a key outcome of initiating cost conversations.

To address the gap between guidelines, needs, and practice, in this study, we will train urologic surgeons in the use of a conversation-based decision aid containing cost-related resources to discuss costs when engaging in shared decision-making (SDM) for slow-growing (also called low-risk) prostate cancer. We will examine the resulting frequency and content of cost discussions between urologic surgeons and patients as they discuss this preference-sensitive treatment decision in the context of SDM. Results can provide insights into how to address cost conversations during SDM about cancer care more broadly.

## Objectives

### Aim 1

We aim to assess the impact of a conversation-based decision aid (Option Grid) containing cost information about slow-growing prostate cancer management options, combined with a brief training session for the urologic surgeon, on the frequency and quality of patient-urologic surgeon cost conversations. We will measure frequency of cost conversations, initiator of cost conversations, and whether or not a referral is made to address costs. We hypothesize that:
1.1: Urologic surgeons assigned to training and use of the decision aid will engage in more frequent cost conversations than urologic surgeons in usual care.1.2: Urologic surgeons assigned to training and use of the decision aid will be more likely than patients to initiate cost conversations. Patients will be more likely than urologic surgeons to initiate cost conversations in usual care.1.3: Urologic surgeons assigned to training and use of the decision aid will be more likely to make a referral to address specific cost details than urologic surgeons in usual care.1.4 (exploratory): Patients of urologic surgeons assigned to training and use of the decision aid will have lower financial toxicity at three-month follow-up than patients of urologic surgeons in usual care.

### Aim 2

We aim to examine the impact of the conversation-based decision aid and surgeon training on decision quality, including measures of decisional conflict, decision regret, and shared decision-making. We hypothesize that:
2.1: Patients of urologic surgeons assigned to training and use of the decision aid will report less decisional conflict, less decisional regret at three-month follow-up, and more SDM than patients in usual care.

## Methods

### Design

This study uses a stepped-wedge cluster-randomized trial design (see Fig. 1) [19]. There are four sequences, with at least one cluster (urologic surgeon) randomized to each sequence. The fifth urologic surgeon will be assigned to the second sequence in order to balance patient accrual to the intervention and control arms. There are five periods, each lasting 3 months, for a total study duration of approximately 15 months. Independent eligible patients will be enrolled at each period within a cluster (urologic surgeon).

**Fig. 1 Fig1:**
[figure not shown]
Study overview

We clustered intervention assignment at the urologic surgeon level because the intervention includes urologic surgeon training and is designed to impact clinical communication patterns, which are reflected in the study outcomes. This clustering approach will minimize the likelihood of contamination between study arms that could occur with patient-level randomization.

The staggered assignment of participating urologic surgeons to the intervention arm has several advantages. The stepped-wedge design allows more surgeons to undergo training in use of the decision aid intervention than would a parallel trial design with a usual care control arm. This is an advantage in the context of strong interest in learning about decision aids in the participating study setting paired with evidence that decision aids improve patient-centered care [20]. Additionally, the staggered timing of surgeon training will facilitate its scheduling within busy clinician timetables. This improves overall study feasibility while ensuring a consistent intervention dose for all participating surgeons.

### Setting

We will conduct this study in outpatient practices affiliated with a large academic medical center. These participating practices are located in a single metropolitan area in the Midwest region of the USA. Decision aids were not routinely used in the participating practices prior to study participation.

### Participants

#### Included urologic surgeons

We will recruit five urologic surgeons who routinely discuss management options for slow-growing prostate cancer with patients.

#### Included patients

We will recruit up to 200 patient participants based on projected volume of eligible patients during each period. Eligible patients include adults visiting a participating urologic surgeon to discuss management options for a first-time diagnosis of slow-growing prostate cancer. Slow-growing prostate cancer diagnoses will initially be defined by a Gleason score of 6 or 7 (3 + 4) and/or prostate-specific antigen (PSA) level less than 10 ng/ml, and/or as confirmed by a surgeon’s referral prior to patient recruitment. Eligible patient visits may occur in-person or by telehealth. We will exclude patients who cannot give informed consent due to cognitive or emotional barriers, and those who are discussing recurrent or ongoing prostate cancer management. Patients seen in these practices are from urban, suburban, and rural settings (approximately 14% from rural settings and approximately 25% from a medically underserved area). Patients in these practices are racially diverse, with approximately 20% identifying as Black or African American, 3% identifying as Hispanic of any race, and 4% identifying as two or more races.

### Intervention

This study tests a two-part intervention: (1) use of an Option Grid conversation-based decision aid by urologic surgeons and patients during their first consultation about managing slow-growing prostate cancer and (2) brief urologic surgeon training in shared decision-making, patient-facing financial resources, and best practices for conversation-based decision aid use.

#### Option Grid conversation-based decision aid with cost information

The Option Grid decision aid is a table with side-by-side comparisons of management options for slow-growing prostate cancer (specified in Table 1), organized as responses to patients’ frequently asked questions [21]. Written at a sixth grade reading level, the grid was developed, tested, and validated using a systematic process including evidence summarization and stakeholder input [21–23]. This type of decision aid is not designed to be comprehensive, but to supplement clinicians’ explanations [24]. For this study, we have added two types of cost information to the Option Grid: (1) general descriptions of relative costs [25] for each treatment/management option (see Tables 1 and 2) a list of general and local resources for navigating cancer care costs. Participating urologic surgeons will deliver the Option Grid intervention at the individual patient level.

**Table 1 Tab1:** Relative cost information added to the Slow-Growing Prostate Cancer Option Grid

Option	Included relative cost information
Monitor with tests	Costs include testing at least once a year. Check your insurance for your exact costs. $-$$
Prostatectomy	Costs include surgery and hospital stay, up to 3 days. Check your insurance for your exact costs. $$$
Radiation (external beam radiation therapy or brachytherapy)	Check your insurance for your exact costs. *External beam radiation*: $$$ *Brachytherapy:* $$-$$$
**Included cost resources**	
Health insurance can help cover some of your care costs. Whatever type of insurance you have, you want to get the most from your plan. You should call your plan to find out things like: • Does my plan cover the care I need? • Are the hospital and doctors who will be treating me part of my plan’s network? • Does my plan cover the facility fee? If so, how much of the fee is covered? • Do I need to be pre-approved by the insurance company before getting this care? • How much of my deductible have I met? How much of my deductible is left before I meet it? • What will be the copay or coinsurance for the treatment I need? In many cancer centers, social workers or navigators can help patients find information about costs or apply for help paying your bills. They can also help if you need a way to get to and from treatment, short-term housing, or have problems with your job because of your care. For more information or to reach a social worker at [cancer center name], you can call [phone number]. This website also has resources for patients at [cancer center name], including how to apply for more help paying your bills. [Web address for cancer center’s patient support services]

**Table 2 Tab2:** Study data summary

Domain (measure)	Source	Timing
**Primary outcomes**		
Frequency of cost conversations (adapted Politi [14]/Hunter [26] checklist)	Patient report; observation	Immediately post-visit
Initiator of cost conversations (adapted Politi [14]/Hunter [26] checklist)	Patient report; observation	Immediately post-visit
Referral to address costs (adapted Politi [14]/Hunter [26] checklist)	Patient report; observation	Immediately post-visit
**Secondary outcomes**		
Shared decision-making (collaboRATE [27])	Patient report	Immediately post-visit
Effort made to compare costs of treatment options	Patient report	Immediately post-visit
Clinical communication (CAHPS communication composite [28])	Patient report	Immediately post-visit
Decisional conflict (SURE [29])	Patient report	Immediately post-visit, 3 months post-visit
Decision regret (Decision Regret Scale [30])	Patient report	3 months post-visit
**Exploratory outcomes**		
Financial toxicity (COST [31, 32])	Patient report	Immediately post visit; 3 months post-visit
**Implementation and acceptability outcomes**		
Attitudes toward SDM (Continuing Professional Development Reaction Scale [33])	Clinician report	Beginning of study period; end of study period
Feasibility of sustained cost conversations and Option Grid use	Clinician report	End of study period
Acceptability of cost conversations and Option Grid use (adapted Ottawa Acceptability Scale [34])	Clinician report	End of study period
**Other data**		
Treatment choice	Patient report	Immediately post-visit
Treatment received	Electronic health record	3 months post-visit
Health literacy (Single-Item Literacy Screener [35])	Patient report	Immediately post-visit
Patients’ other (comorbid) health conditions	Electronic health record	Immediately post-visit
Patients’ demographic characteristics	Patient report	Immediately post-visit

#### Option Grid training

At the start of the study, urologic surgeons will be trained in the study protocol. At the start of their active arm assignment, each surgeon will complete a survey about their attitudes relating to SDM and will be trained in use of the Option Grid, including discussing costs with patients. Option Grid training will (1) present a model of SDM [36] and best practices for use of the Option Grid; (2) share details about incorporating cost discussions into SDM; (3) provide each surgeon with a list of cost-related resources and referrals for patients, including ways to lower out-of-pocket costs; and (4) include a mock patient simulation to allow the urologic surgeon to practice using the intervention. The study’s principal investigator ([name]) and co-principal investigator (GE) will deliver the Option Grid training at the cluster level.

### Outcomes

#### Primary outcomes

We will measure the frequency of cost conversations, initiator of cost conversations, and whether or not a referral is made to address costs. We will collect these primary outcomes by patient report from all participating patients in a questionnaire completed immediately post-visit (or shortly after a telehealth visit).

We will also use an existing observer checklist [14] to assess these outcomes for participating patients who consent to audio-recording their clinic visits. We will use Hunter et al.’s approach to defining a cost discussion: “any mention of the patient’s out-of-pocket expenses or insurance coverage for a past, present, or potential health care service” [26]. For example, any mention of costs or insurance coverage for primary surgery, radiation, imaging, as well as indirect costs of care such as time off work, transportation, recovery time, will be documented and included in our analyses. If direct or indirect costs are mentioned per Hunter’s definition [26], we will indicate that costs were discussed during the consultation. If there are two mentions of cost in one transcript, with a different topic in between, the mentions will be coded as two cost discussions. If costs are discussed at all, the subsequent items (length of time of the cost conversation, number of times cost was discussed, who initiated the cost discussion, content of cost discussions, whether a referral is made to address costs) will then be evaluated. We will document references to the Option Grid to examine whether the Option Grid directly prompted the cost conversation. Because we do not expect surgeons to know specific details about treatment costs, the checklist also includes an item to measure whether a referral is made to address more detail about costs. We will document to whom a referral is made (navigator, social worker, outside resource).

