### Sample size

We assume given the study timeline and projected patient volumes that it is feasible to recruit up to 50 patients from each of the five participating urologic surgeons, to target a total of 200 patient participants. Due to the novelty of our shared decision-making intervention intended to promote cost conversations in cancer care, limited data were available to inform the assumed ICC [14]. Based on the unmeasured clinician-level variability observed in other studies using similar interventions to study different outcomes, we conservatively assumed a relatively large ICC value of 0.05. Under these assumptions, and assuming an intraclass correlation coefficient of 0.05 for our primary outcome, the design effect of the stepped-wedge design equals 3.12, making the effective sample 32 per intervention group; this is the equivalent sample-size under a design in which there is no clustering of patients within surgeons [40].

In relation to Aim 1 and our primary research questions, prior research demonstrates that surgeons who used an encounter decision aid about early-stage breast cancer surgery with comparative cost information were far more likely to engage in cost conversations compared to those using a decision aid without cost information or those in usual care (66.7% versus 33.3%) [14]. Surgeons in the cost information decision aid group were also more likely to initiate these conversations compared to those in the non-cost information decision aid group (86.4% versus 34.1%) [14]. We estimated power directly for a stepped-wedge design. A requirement for performing this calculation is supplying the between-cluster variance. We estimated this quantity by solving for its value given the specified ICC of 0.05 and the within-cluster variance of a Bernoulli (binary-valued) random variable, whose mean equals the average value of the assumed probabilities of the outcomes for the two comparison groups (0.5, the most conservative value we could assume). The resulting power for a two-sided test was estimated to be 0.804. A projected sample size of 200 is therefore sufficient to answer our primary research questions.

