### Analysis

We will perform unadjusted bivariate comparisons of outcomes and predictors across intervention groups using t tests for continuous variables and chi-square tests for categorical variables. We will also conduct analysis adjusting for patient demographic characteristics, patient clinical characteristics, and the time period when the patient began follow-up. We will use logistic regression to model the Aim 1 primary outcome of whether or not a cost conversation occurred. In Aim 2, we will use linear regression to analyze outcomes with multi-level scales (e.g., decision regret scale [30]) and logistic regression to analyze binary outcome measures (e.g., collaboRATE [41]). To account for clustering of patient participants by urologic surgeon, we will estimate hierarchical models with urologic surgeon random effects. Let *Y*_*ijt*_ denote an outcome measured on the *i*th patient of the *j*th surgeon at time *t* and *OG*_*jt*_ indicate whether surgeon *j* has transitioned from usual care to the Option Grid (OG) by time period *t*. To lessen the reliance on the random assignment of surgeons to step times to balance any changes across time between the intervention groups, we adjust for the time period when the patient began follow-up, patient demographic and patient clinical characteristics. Adjustment for time period will be enabled by including indicator variables for time periods 2 through 5 (making time period 1 the excluded category) with effects denoted by {*λ*_*t*_}=_*t* = 2 : 5_ while all other patient-level variables will be included in a vector of covariates, denoted *X*_*ijt*_. Therefore, the model for the Aim 1 analysis and those outcomes modeled as binary random variables in Aim 2 has the form
1$$ logit\left(\Pr \left({Y}_{ijt}=1\left|{\theta}_j\right.\right)\right)={\beta}_0+{\beta}_1{OG}_{jt}+{\beta}_2{X}_{ijt}+{\lambda}_t+{\theta}_j $$

while the model for those outcomes modeled as continuous variables in Aim 2 has the form
2$$ {Y}_{ijt}={\beta}_0+{\beta}_1{OG}_{jt}+{\beta}_2{X}_{ijt}+{\lambda}_t+{\theta}_j+{\varepsilon}_{ijt} $$

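### Three outcomes are listed as primary, each from two sources, but the power figure covers only occurrence of a cost conversation in all 200 patients, while 200 is called sufficient for every primary question

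*Protocol article*

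**What the plan says.** The Abstract states: "Primary outcomes include frequency of cost conversations, initiator of cost conversations, and whether or not a referral is made to address costs". The Primary outcomes section repeats the same three: "We will measure the frequency of cost conversations, initiator of cost conversations, and whether or not a referral is made to address costs". Table 2 lists all three under its primary heading, each with the source entry "Patient report; observation".

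The two sources cover different patients. On patient report: "We will collect these primary outcomes by patient report from all participating patients in a questionnaire completed immediately post-visit". The observer checklist is used to "assess these outcomes for participating patients who consent to audio-recording their clinic visits". That checklist is also conditional: "If costs are discussed at all, the subsequent items" are scored, and initiator and referral are among those items.

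The Analysis section names one outcome: "We will use logistic regression to model the Aim 1 primary outcome of whether or not a cost conversation occurred". The Sample size section also speaks of a primary outcome in the singular when it sets the intraclass correlation. It gives one power figure, 0.804, and concludes: "A projected sample size of 200 is therefore sufficient to answer our primary research questions".

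**The concern.** The article gives two answers to the question of what is primary: three outcomes in the Abstract, Table 2 and the Primary outcomes section, and one in the Sample size and Analysis sections. It also leaves open which source decides if patient report and coded audio disagree. They may well disagree by arm. Patients are not blinded, and in the intervention condition they receive a decision aid with cost text before the visit (Randomization; Option Grid delivery), which could colour what they report.

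Two things are at stake. If outcome and source are not fixed beforehand, they can be chosen after the results are known. And a reader would take the sufficiency sentence as covering all three outcomes from both sources, when the calculation behind it covers one outcome in one population.

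**Working it through.** **Inputs from the article.** N = 200; intraclass correlation 0.05; 66.7% versus 33.3% for a cost conversation, mean 0.5; 86.4% versus 34.1% for surgeon initiation; design effect 3.12; four sequences, five periods, five surgeons with the fifth in sequence 2; power 0.804, two-sided. **Assumed, because not stated:** alpha 0.05; the share consenting to recording.

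**Formula (Hussey-Hughes, period effects included).** With I clusters, T periods, s² = within-cluster variance / patients per cluster-period, t² = between-cluster variance, U = number of treated cells, W = sum of squared treated counts by period, V = sum of squared treated counts by cluster:

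Var = I·s²·(s² + T·t²) / [(I·U − W)·s² + (U² + I·T·U − T·W − I·V)·t²]

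Power = Φ(0.334/SE − z), with z = 1.960 at 5%.

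**1. The article's own figure.** Within-cluster variance is 0.5 × 0.5 = 0.25, so t² = (0.05/0.95) × 0.25 = 0.01316. For four clusters × 5 periods × 10 patients: s² = 0.025, U = 10, W = V = 30.
- Var = 4 × 0.025 × (0.025 + 0.0658) / (10 × 0.025 + 30 × 0.01316) = 0.00908 / 0.6447 = 0.01408; SE = 0.1187.
- Power = Φ(2.815 − 1.960) = **0.804**, as stated.
- The planned five surgeons × 5 periods × 8 patients (U = 13, W = 51, V = 39) give 0.781, or 0.801 if 0.25 is read as total variance.
- The effective sample also reproduces: 100/3.12 = 32 per group.

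The mean of 0.5 identifies the outcome. It is the average of 66.7% and 33.3%, whereas the initiator rates average (86.4 + 34.1)/2 = 60.25%.

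**2. Audio-coded conversation outcome.** Same formula, five surgeons, alpha 0.05, with 8 patients per cell multiplied by the consenting share. The range spans the two readings of 0.25.

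| Consent (assumed) | Patients per cell | Power |
|---|---|---|
| 80% | 6.4 | 0.70-0.72 |
| 70% | 5.6 | 0.65-0.67 |
| 50% | 4.0 | 0.52-0.54 |

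The four-cluster layout gives 0.72, 0.67 and 0.55.

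**3. Initiator.** It is defined only where a conversation took place. With about 100 patients per condition, that is 100 × 0.333 + 100 × 0.667 ≈ 33 + 67 = 100 patients. Spread evenly (a simplification), this is 4 per surgeon-period. With difference 0.864 − 0.341 = 0.523 and variance 0.6025 × 0.3975 = 0.239, power is about 0.90 for five surgeons and 0.91 for the four-cluster layout.

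**4. Referral.** The article gives no rate for either condition, so no power can be computed.

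**5. Multiplicity, if the three outcomes are tested as co-primary without adjustment.** Independent tests: 1 − 0.95³ = 0.143, less if positively correlated. With a Bonferroni split, alpha = 0.05/3 = 0.0167 and z = 2.394, so power on the conversation outcome is Φ(2.815 − 2.394) = 0.66, down from 0.804.

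**The case against.** Only a condensed article is at hand, and a multiplicity rule may well stand in the analysis plan. That is right, and the absence of such a rule is not the point here. An unseen plan would not, however, reconcile an article that states both three primary outcomes and one, nor narrow a sufficiency sentence that is wider than its calculation.

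The article does lean one way. It models occurrence of a conversation, and it introduces the observer checklist as an addition to patient report. That is a hint, but Table 2 sets the two sources and three outcomes level.

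The sufficiency sentence is also not unfounded throughout. An initiator effect is cited, and it is large enough that about 100 evaluable patients would do. Two limits apply: those rates compare two decision-aid groups and not an aid with usual care, and the check above compares conditions, whereas hypothesis 1.2 sets surgeon against patient initiation within each condition.

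A reader might multiply three outcomes by two sources and infer six primary tests with a 26% chance of a false positive (1 − 0.95⁶ = 0.265). The documents do not support that. Nowhere are six tests stated, the two sources record the same visit, and the observer items depend on one another, so independence is implausible. Nor does the article say that any one positive result means success; hypotheses 1.1, 1.2 and 1.3 are stated separately.

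**Conclusion.** The point stands as an internal inconsistency together with an over-wide claim. The figure of 0.804 is reproducible, but only for occurrence of a cost conversation, in all 200 patients, with one two-sided test at an assumed 5%. It does not extend to the audio-coded version (about 0.70-0.72 down to 0.52-0.54 over assumed consent of 80% to 50%), and it has no basis for referral. Initiator is plausibly powered at about 0.90, so it would be wrong to infer that every outcome beyond the first is underpowered. Testing three co-primary outcomes without adjustment would carry up to about 14% false-positive risk with independent tests; splitting alpha by three would leave power of about 0.66.

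The consent shares are illustrative, and all power values use the same kind of large-sample approximation as the article. A reader might also infer from the five-surgeon value of 0.781 that the stated power is wrong. The article does not give enough detail for that, since the total-variance reading returns 0.801.

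**What to change.** Before results are seen:

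- Name occurrence of any cost conversation as the single primary outcome, and state which source decides. Patient report is the only source covering all 200. If it is chosen, acknowledge the risk that unblinded patients' reports are coloured by the cost text. Do not claim that the 66.7% and 33.3% rates are themselves patient-reported: the article does not show this, and it describes the instrument from that study as an observer checklist.
- Test initiator, as defined in hypothesis 1.2, and then referral in a fixed sequence at two-sided 5%, and state that alpha.
- Report the other source as a supportive analysis, with patient-observer agreement by arm.
- Limit the sufficiency sentence to the cost-conversation outcome in all 200 patients, and say that power for referral and for the recorded subset was not established.

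No alpha is lost on the powered outcome and no further patients are needed. The costs are that initiator and referral become formally dependent on the first test, and that the change must be recorded as an amendment, because recruitment began on 24 June 2020 (Trial status).
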